## Abstract

**Background**: Stroke is the leading cause of physical disability in adults in Catalonia. Despite this, there is a lack of evidence of physiotherapy interventions on functional capacity during the chronic phase of the pathology. This multicenter clinical trial will be conducted with a sample size of 75 participants. **Objectives**: The objective of the study is to evaluate the effectiveness of a therapeutic exercise program in physiotherapy using telerehabilitation to optimize functional recovery and quality of life in people with chronic stroke, and to determine its impact on adherence to the exercise program. **Methods**: This is a multicenter randomized controlled trial. Three parallel groups will be compared, and two will undergo the same type of therapy. A control group (CG) will perform conventional intervention in primary care. There will be two experimental groups; (EG1) will perform document-guided therapeutic exercises at home and (EG2) will perform therapeutic exercises at home guided by a telerehabilitation program. The outcomes to be measured are degree of independence of a person in their activities of daily living, assessed by the Barthel Index, motor function, muscle tone of the affected limbs, muscle strength of the affected limbs, balance, gait efficiency, perception of musculoskeletal pain, perception of fatigue, risk of falls, perception of quality of life, and the perception of perceived subjective change after treatment. These outcomes will be evaluated at baseline (T0), at ten weeks (T1) (end of the intervention), and at 18 weeks (T2). The study duration per patient will be 18 weeks (a ten-week intervention, followed by an eight-week intervention follow-up). The analysis will be performed using a mixed linear model (ANOVA 3X3) and significance level *p* < 0.05.

## 1. Introduction

Stroke is the leading cause of physical disability in adults in Catalonia, Spain [1]. The incidence in Catalonia is 175 cases per 100,000 inhabitants, representing 11,500 new cases per year [2]. In Europe, a 34% increase in stroke cases is expected in the coming years [3]. In Catalonia, new cases represent an average cost to the health system of 315 million euros per year [4]. Furthermore, stroke accounts for EUR 1109 million per year in informal care costs [5]. The progress made in the treatment of the acute phase, through the Stroke Code, the management of patients in Stroke Units and reperfusion therapies in acute ischemic stroke, has improved the functional prognosis of surviving patients [6]. However, the available data on the physical and emotional health sequelae experienced by patients in the chronic phase [4] illustrate the significant impact on people’s health: 77% report poor perceived health; 55.7% have walking difficulties and 52.2% struggle with activities of daily living [7]; 71.6% experience constant pain [8]; and 40% present with limb spasticity [9].

At present, there is no evidence of the finiteness of the cerebral somatotopic organization [10]. On the other hand, the existing mechanisms for its reconfiguration and adaptation based on synaptic adaptation are described [11]. Studies have shown that, although the highest level of resilience is found in the subacute phase of the pathology, between 30 and 90 days post-stroke, the brain can also be reorganized through residual plasticity in the chronic phase even if the efficiency of neural network transfer is reduced [12,13,14]. Axonal sprouting and dendritic remodeling are key processes of neuronal resilience that continue to occur during rehabilitation, even beyond the first year after stroke [15]. Neurotrophins play a crucial role in neuroplasticity, neurogenesis, and neuroprotection of the Central Nervous System. The upregulation of neurotrophin expression contributes to the prevention and recovery of neurotrophin disorders. Therapeutic exercise is one of the tools physiotherapists use for enhancing the expression of neurotrophic factors in the motor regions of the brain during rehabilitation [15,16,17]. It is a comprehensive mechanism for addressing specific sequelae, the clinical situation, and therapeutic objectives, structuring the activity according to the optimal dosage of each patient [18].

The Rehabilitation Plan of Catalonia, Spain, an instrument that promotes a biopsychosocial approach to the person-centered care process [19,20], and indicates that the overall provision of rehabilitation care after having suffered a stroke must be continuous: community rehabilitation services must guarantee optimal rehabilitation, to achieve the best functional level and quality of life for the post-stroke patient. On the other hand, it establishes that outpatient and/or home-based rehabilitation for patients in the chronic post-stroke phase is indicated only in cases with a notable deterioration in functional status, or when a complication related to an underlying condition has occurred [19,20]. In practice, the system does not contemplate any intervention in the chronic post-stroke phase that guarantees continuity.

The study conducted by the Stroke Alliance for Europe reports that the rehabilitation received by stroke survivors in Europe is not intense enough, is too short, and often does not address the ongoing problems arising from the pathology [21]. In addition, it also states that long-term support is often non-existent [21]. The Spanish Society of Neurorehabilitation, in its proposal for a model for the care of acquired brain injury published in 2021, states that the duration of the necessary treatment should not be subject to time limitations but should be conditioned to the patient’s response to treatment and the possibilities of improvement of the patient after stroke [22].

To address these limitations, technology-based rehabilitation interventions have been developed in recent decades, showing promising results in improving functional mobility and independence in stroke patients, including telerehabilitation [23,24,25,26]. The use of technology promotes repetitive and task-specific training, active patient participation, integration of constructive and concurrent feedback, and accurate measurement of functional improvement [23]. The latest updates of the Clinical Practice Guidelines recommend the use of telerehabilitation as evidence of its benefit on quality of life [27].

The COVID-19 pandemic further revealed the advantages of telerehabilitation, such as greater accessibility, participation, co-responsibility and personalization of treatment [28,29]. However, the current model of stroke recovery in Catalonia is subject to time limitations that can lead to a worsening of the patient’s degree of disability and quality of life.

The objective is to evaluate the effectiveness of a therapeutic exercise program in physiotherapy using telerehabilitation to optimize functional recovery and quality of life in people with chronic stroke. In addition, the study aims to determine whether the telerehabilitation format improves adherence to the therapeutic exercise program compared with the paper-based delivery method.

## 2. Materials and Methods

### 2.1. Study Design and Setting

This study is an assessor-blinded, multicenter trial with a ten-week treatment period followed by a two-month follow-up. It follows the consensus-based core recommendations from the stroke recovery and rehabilitation expert group [18], thereby improving the study’s development and the SPIRIT statement [30]. This study has been approved by the Research Ethics Committee of the Institut d’Investigació en Atenció Primària Jordi Gol (IDIAP Jordi Gol) (num. 24/190-P). It has been registered at ClinicalTrials.gov (NCT06944197). Participants will be randomly allocated in a 1:1:1 ratio to the control group (CG) (*n* = 25) or the experimental groups (EG1) (*n* = 25); (EG2) (*n* = 25). Patients are being recruited by five primary care centers of the Southern Metropolitan Management of the Institut Català de la Salut (ICS) in Catalonia, Spain.

### 2.2. Recruitment and Blinding

Participants will be randomly assigned to one of the three intervention groups using a computer-generated sequence through Random.org. To ensure allocation concealment, only the principal investigator (PI) will have access to the randomization list. This allocation will take place after obtaining informed consent, but before baseline assessments (T0), and the allocation will not be disclosed to the physiotherapists or outcome assessors until the participant has been formally enrolled in the study.

Although no stratification or block randomization procedures were applied, rigorous measures have been implemented to minimize potential bias and ensure the internal validity of the study. Outcome assessments will be performed by independent, previously trained physiotherapists acting as blinded assessors. In addition, statistical analyses will be conducted by researchers blinded to group allocation, thereby strengthening the objectivity of the results. All data will be recorded in a secure digital system, password-protected and accessible only to authorized members of the research team.

Prior to the randomization process, participant recruitment will follow a series of steps designed to ensure ethical transparency and informed understanding. First, the principal investigator, together with the physiotherapist responsible for each assigned center, will provide detailed information to collaborating healthcare professionals regarding the inclusion and exclusion criteria, as well as the general characteristics of the study. Second, physiotherapists from the research team will contact potential participants by phone through their primary care center to explain the purpose, design, duration, and potential risks and benefits of the study. If a patient expresses interest, a face-to-face appointment will be scheduled to provide more detailed information and resolve any questions. Informed consent will be obtained during this appointment, prior to accessing the participant’s medical history, in compliance with ethical standards and data privacy regulations.

After group allocation and before starting treatment (T0), pre-intervention tests will be conducted to assess the baseline values of the primary and secondary outcome measures. A maximum of one week after completion of the intervention (T1), data will be collected for all efficacy outcomes (see Section 2.5). The same data will be collected two months after the end of the intervention (T2) (Figure 1). During the ten weeks of intervention, data will be collected in each session regarding adherence to the intervention (number of sessions and duration), intensity, exercises performed by each patient, and any incidents. All visits and efficacy evaluations will be conducted at the patient’s reference primary care center with the corresponding evaluating physiotherapist.

The study uses a single-blind design due to the nature of the interventions; therapists and participants cannot be blinded to treatment allocation. To avoid detection bias, efficacy outcomes will be assessed by an independent, blinded evaluator. Each center has a trained physiotherapist assessor, supervised by the principal investigator. The training information is available online and in paper format. Additionally, all statistical analyses will be conducted by researchers blinded to group allocation.

All data will be recorded in an online document shared by all the evaluators of the research team. A form created in a spreadsheet will be used. All researchers are trained in the use of the scales and the document, and they have a help guide, as well as a consultation service directly with the principal investigator of the study who is responsible for the logistics of the study. Access to the study registration document is restricted to authorized study personnel via password.

Furthermore, all data management procedures comply with the General Data Protection Regulation (GDPR) and the information security policies of the Institut Català de la Salut (ICS). Study data will be stored on ICS institutional servers, which implement standardized security and access-control measures. Access to the study data will be restricted to authorized research personnel using institutional credentials. Personal identifying information is not included in the study’s analytical database; instead, it is kept separately within ICS systems, and each participant is assigned a unique study identification code to ensure pseudonymisation. Remote and digital data collection is carried out using secure institutional platforms that guarantee data confidentiality and integrity throughout the study.

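### The sole holder of the randomisation list also briefs referrers and supervises the blinded assessors, and the protocol describes no separation between these roles

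*Protocol article*

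**What the plan says.** Section 2.2 (Recruitment and Blinding) of the protocol article describes a computer-generated sequence without blocks or strata. The stated means of concealment is that "only the principal investigator (PI) will have access to the randomization list". Allocation follows informed consent and precedes the baseline assessment. It is withheld from physiotherapists and assessors until the participant is formally enrolled.

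The same section gives the principal investigator three further tasks:

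- The opening recruitment step: "First, the principal investigator, together with the physiotherapist responsible for each assigned center, will provide detailed information to collaborating healthcare professionals". The information covers the eligibility criteria and the general features of the study.
- Oversight of outcome assessment: "Each center has a trained physiotherapist assessor, supervised by the principal investigator".
- Support to the researchers. After stating that they are trained in the scales and the data form, the section says that "they have a help guide, as well as a consultation service directly with the principal investigator of the study".

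Section 2.7 adds that serious adverse events go at once to the principal investigator, who also oversees safety monitoring.

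Section 2.2 nevertheless states that "efficacy outcomes will be assessed by an independent, blinded evaluator".

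**The concern.** Concealment works when whoever knows the next assignment is kept away from the process that brings participants in. Assessor blinding works when whoever knows the arm is kept away from the process that produces the ratings. Section 2.2 treats restricting the list to one person as enough for the first aim. It does not matter much how few people hold the list if the one holder also works on recruitment and outcome assessment.

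Two safeguards are at stake. The first is comparability of the arms at entry, which foreknowledge can undermine through the choice or timing of entrants. The second is protection of the ratings. Participants and therapists cannot be blinded here, as section 2.2 acknowledges, so the assessor's blinding is the main defence against detection bias. That covers the primary outcome, the Barthel Index, and the other clinical rating scales in section 2.5.

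**Working it through.** No formula decides this point. The check sets the stated roles side by side.

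1. **Who can see the assignments?** Only the principal investigator (section 2.2). The list is generated by computer and covers the planned 75 participants, 25 per arm (section 2.1).
2. **Who brings participants in?** The principal investigator and the centre physiotherapist brief the collaborating professionals. After that, "physiotherapists from the research team will contact potential participants by phone through their primary care center". A face-to-face appointment follows, at which consent is taken. The person taking consent is not named. The principal investigator is thus part of recruitment at the level of the centres, and is not described as acting on individual patients.
3. **Who stands behind the ratings?** Each centre's assessor does the rating. The principal investigator supervises that assessor and provides the consultation service. The service appears in the sentence about training in the scales and the form, so it is a fair inference that it covers how a scale is applied. The text does not say that it covers the score of a particular participant.
4. **Is there a barrier between role 1 and roles 2 and 3?** None is described. The article mentions no independent list holder, central allocation service or envelopes, and no rule that sends assessors' queries to someone unaware of the arm.
5. **Does another route bring the arm to the same person?** Yes. Serious adverse event reports reach the principal investigator directly (section 2.7), and in a trial with unblinded participants and therapists such a report can reveal the arm. Moving the list alone would not close that route.
6. **Size.** The documents give no figure from which a bias could be computed. As an illustration only, suppose k participants in an arm of 25 were each scored d Barthel points too high. The arm mean would shift by k × d / 25. With an assumed d = 10:
   - k = 1: 10 × 1 / 25 = 0.4 points
   - k = 5: 10 × 5 / 25 = 2.0 points

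   Section 2.3 cites a minimal clinically important difference of 1.85 and a planned difference of about 8–10 points. The second case would exceed 1.85 and equal 2.0/10 = 20% to 2.0/8 = 25% of the planned difference. Neither d nor k comes from the documents. The sum shows only how sensitive a mean of 25 is, and the conclusion does not rest on it.

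**The case against.** The case for the plan has substance.

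- **Entry.** Briefing professionals on criteria is information given at centre level. Those who telephone patients do not know the coming assignment, and disclosure waits until formal enrolment. A reader might infer that the list holder can steer who enters. The article does not support that, because it never describes the principal investigator as screening, consenting or enrolling. This part of the objection stands.
- **Scoring.** A reader might infer that an unblinded person advises on individual scores. The text describes a general help service on scales and a spreadsheet form, attached to someone responsible for logistics. It reports no advice on a given participant and no disclosure of an arm. This also stands.
- **Disclosure to assessors.** Withholding allocation from assessors until enrolment might be read to mean that they are told the arm afterwards. The section elsewhere calls them blinded without such a limit, so that reading is not established, and the present point does not need it.
- **Condensed article.** The full protocol may describe how assignments are released. That would excuse a missing detail. It does not remove roles that the article itself states and combines: the list, the referrer briefing and the supervision of assessors belong to one person, and sole access by that person is offered as the safeguard.

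The Limitations section discusses unblinded therapists and unequal contact between arms, and relies on blinded assessors as a protection. It does not mention this combination of roles.

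**Conclusion.** The point holds as one of role separation. The person who can see all allocations is also engaged in recruitment and supervises and advises the assessors, and the article describes nothing that keeps these functions apart. The stated concealment device, and the description of the assessors as independent, are therefore weaker than presented. The assessor side is the stronger part. The recruitment side shows only that the separation is missing.

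The documents show no selective entry, no biased score and no unblinding, and they permit no estimate of bias. The conclusion assumes that the roles are carried out as section 2.2 states them and that no further barrier stands in the full protocol. It is worth acting on because the correction is cheap and recruitment, according to section 2.1, is under way, so the remaining allocations can still be protected.

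**What to change.** For the remaining allocations:

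- Move the list to a person already in the institution who has no part in recruitment, treatment or assessment. Alternatively, use an electronic randomisation module, or sealed, opaque, numbered envelopes prepared by such a person. Release one assignment after each consent and enrolment.
- Do not give the principal investigator the list or individual allocations while that role supervises and advises assessors.
- Where the principal investigator must learn an arm, for example through a serious adverse event report, send scale queries about that participant to a team member who does not know the arm.
- State these arrangements in section 2.2, and report how many participants had been allocated before the change.

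Interventions, visits and sample size stay as they are. The cost is a short written procedure, a named colleague for the occasional redirected query, and a brief delay at each allocation. This assumes that the institution has someone uninvolved who can hold the list. Allocations already made cannot be protected afterwards, which is why their number should be reported.

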### 2.3. Sample Size

The sample size was calculated using an a priori power analysis conducted with G*Power software (version 3.1.9.7). The calculaion was based on a mixed-design repeated-measures ANOVA with one between-subjects factor (three groups) and one within-subjects factor (three time points). A conservative medium effect size (f = 0.32) was selected for the calculation, which represents a smaller effect than that reported by Aphiphaksakul et al. [31], who reported functional improvements following a mobili-application-based training protocol in stroke patients. This effect size corresponds to an expected between-group difference of approximately 8–10 points on the Barthel Index, substantially exceeding the established MCID of 1.85 [32,33], thereby ensuring clinically meaningful differences. The analysis employed a significance level of α = 0.05 and a statistical power of 0.80 (1 − β = 0.80), and 10% dropout rate. Based on these parameters, the required sample size was determined to be 75 participants, with 25 participants allocated to each group.

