### 2.8. Statistical Analysis

The statistical analysis will be performed with the IBM SPSS v.26.0 software. Descriptive statistics will be calculated for all variables. To check the normal distribution of the variables, the Kolmogorov–Smirnov test with the Lilliefors correction will be used. For the comparison of the groups, a mixed 3 × 3 ANOVA will be carried out with interaction time (three measurement time points) and group (three intervention groups). The assumption of sphericity will be checked by means of the Mauchly test; if it is not met, the Greenhouse–Geisser correction will be used for interpretation.

The primary outcome and the Key Secondary Outcomes (motor function, muscle tone, muscle strength, balance, and quality of life) will be analyzed following this main model, given their clinical relevance. Additional Secondary Outcomes (gait performance, perceived pain, fatigue, fall risk, and subjective perceived change) will be analyzed using the same statistical approach but interpreted with greater caution due to their supplementary nature.

When a statistically significant effect is observed, the post hoc test will be performed using the Bonferroni correction to adjust for multiple comparisons. This correction will be applied systematically to all post hoc analyses to address the multiplicity of secondary outcomes.

For qualitative variables, the Chi-square test or Fisher’s Exact statistic will be used. The effect size will be calculated using Cohen’s d. Cohen’s coefficients [53] are interpreted as follows: large effect sizes, d > 0.8; moderate effect sizes, d = 0.5–0.79; and small, d = 0.2–0.49. The significance level was established at *p* < 0.05 with a 95% confidence interval. Missing data will be handled using Little’s MCAR test and multiple imputation (MICE) performed separately for each intervention group using the SPSS multiple imputation module. The analysis will be undertaken on an “intent-to-treat” basis.

Adherence outcomes (percentage of sessions completed, weekly frequency, and session duration) will be analyzed descriptively and compared between groups. If appropriate, exploratory analyses (e.g., correlation or regression models) will be conducted to examine the potential mediating or moderating role of adherence in relation to functional outcomes.

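### Random allocation precedes the T0 assessment and nothing ties its release to completion of T0, so baselines can be influenced by knowledge of the arm and participants can be lost before any outcome is recorded

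*Protocol article*

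**What the plan says.** Section 2.2 of the protocol article gives the order of events twice, and both statements agree. The first reads "This allocation will take place after obtaining informed consent, but before baseline assessments (T0"). The second reads "After group allocation and before starting treatment (T0), pre-intervention tests will be conducted to assess the baseline values" of the primary and secondary outcomes.

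On who may know the arm, the same section says that "the allocation will not be disclosed to the physiotherapists or outcome assessors until the participant has been formally enrolled in the study". Only the principal investigator holds the list. It then states that "therapists and participants cannot be blinded to treatment allocation", and that "efficacy outcomes will be assessed by an independent, blinded evaluator".

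Section 2.8 specifies a mixed 3 × 3 ANOVA with "interaction time (three measurement time points) and group (three intervention groups"), so T0 is one of the three time levels. This model serves the primary and key secondary outcomes. The additional secondary outcomes "will be analyzed using the same statistical approach but interpreted with greater caution". The analysis is by intention to treat, with multiple imputation carried out separately in each arm.

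**The concern.** A baseline is safe as a reference point when it cannot depend on the arm. Measuring it before allocation guarantees that. Measuring it after allocation is still safe if nobody involved in the measurement knows the arm, but the protocol does not secure this. The release point is formal enrolment, which is not defined and is not linked to completion of T0. Participants are not mentioned in the restriction at all.

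Two routes to bias follow.

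- **Reactive baselines.** A participant who knows the arm may answer or perform differently at T0. The exposed instruments are the self-reported ones (Brief Pain Inventory, Fatigue Severity Scale, NEWSQOL) and the effort-dependent ones (Timed Up and Go, gait speed). NEWSQOL is a key secondary outcome. A blinded assessor does not prevent this.
- **Loss before baseline.** A participant can leave after allocation and before T0. Controls receive a single consultation and a guide (section 2.6), so a link between arm and early withdrawal is conceivable. Such a person belongs to the intention-to-treat population but has no outcome value at any time point.

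**Working it through.** **1. The plan's own sample size, to see whether the remedy affects it.** Inputs from section 2.3: "A conservative medium effect size (f = 0.32) was selected for the calculation", α = 0.05, power 0.80, 10% dropout, three groups, three times. The correlation between repeated measures is not stated; 0.5 is assumed.

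- Between-groups test: λ = f² × N × 3 / (1 + 2ρ). With N = 66, λ = 0.1024 × 66 × 3 / 2 = 10.14, on 2 and 63 df, and power is 0.80. N = 63 falls short, at 0.78.
- Allowing for dropout: 66 / 0.9 = 73.3, so 74, or 75 for equal groups. The stated 75 is reproduced.
- The interaction test with λ = f² × error df also needs 66. With the other G*Power convention and ρ = 0.5 it needs only 24, or 27 after dropout, which does not reproduce 75.

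The timing of T0 is not an input to any of these formulas, so moving T0 leaves 75 unchanged.

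**2. How a T0 shift enters the test.** Suppose there is no treatment effect and one arm's T0 mean is displaced by b SD. That arm's T0-to-T1 and T0-to-T2 changes are then displaced by the full b in the opposite direction, relative to the other arms. For a displacement of one cell in a 3 × 3 table, the squared interaction effects sum to b² × (2/3) × (2/3) = 4b²/9. With 25 per arm and equal correlation ρ between the time points:

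λ = 25 × (4/9) × b² / (1 − ρ), on 4 and 144 df.

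Example: b = 0.2 and ρ = 0.7 give λ = 25 × 0.444 × 0.04 / 0.3 = 1.48.

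The table gives the simulated type I error of the group × time test (10,000 trials per setting, nominal 0.05). The noncentral F distribution with the λ above agrees to within 0.01 for the rows with b above 0.

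| Assumed shift b (SD) | ρ = 0.5 | ρ = 0.7 | ρ = 0.9 |
|---|---|---|---|
| 0 | 0.050 | 0.050 | 0.047 |
| 0.1 | 0.063 | 0.068 | 0.110 |
| 0.2 | 0.099 | 0.133 | 0.346 |
| 0.3 | 0.165 | 0.270 | 0.701 |

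A shift common to all arms has no effect on this test. Only a difference between arms matters.

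**3. Translation to Barthel points.** The document states no SD. Section 2.3 equates f = 0.32 with a difference of 8–10 points. For three groups, f = 0.32 corresponds to a largest standardized difference of 0.32 × √6 = 0.78 if the means are equally spaced, or 0.32 × 3/√2 = 0.68 if one arm differs from two equal ones. The SD is then between 8 / 0.78 ≈ 10 and 10 / 0.68 ≈ 15. On that assumption, 0.1–0.3 SD is about 1.0–4.5 points, against the cited MCID of 1.85. This is only a scale for reading the table. Nothing in the document says that a shift of this size will occur on the Barthel Index.

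**4. Loss before T0.** One such loss is 1/25 = 4% of an arm. The 10% dropout allowance is 2.5 participants per arm. Imputation within an arm has no outcome value from that person to condition on.

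**The case against.** The strongest reply is that allocation is not disclosure. Only the principal investigator holds the list. Each arm's intervention is explained at an individual consultation (section 2.6), and T0 comes before treatment starts. Participants may therefore learn their arm only at that consultation, after T0. The statement that they cannot be blinded describes the trial as a whole, not their knowledge at T0. If the arm were in fact withheld until T0 was recorded, the reactive-baseline route would be closed. This stands: the text permits early disclosure but does not state it. What remains is that the protocol ties release to enrolment instead of to T0 and says nothing about participants. Concealing the arm until T0 would also not restore outcome data for people who leave in the interval.

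Several stronger readings are tempting, and the document does not support them.

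- **Every comparison is biased.** Adherence has no baseline, and the Global Rating of Change measures perceived change after treatment. Neither has a T0 value that could shift.
- **Assessors know the arm at T0.** The enrolment wording, read literally, would allow it, but assessor blinding is stated in sections 2.1 and 2.2. It lessens the risk for assessor-rated scales, including the Barthel Index.
- **Participants will be excluded after randomization.** No passage says that eligibility scores are taken at T0.
- **The shift exceeds the MCID, or most early losses fall in the control arm.** The document gives no evidence on the size or direction of either. Section 2.6 also offers the platform programme to the other groups if telerehabilitation proves superior, which is some reason to stay.

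The intention-to-treat rule, the imputation by arm and the 10% allowance are relevant, but they do not cure loss that depends on the arm.

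**Conclusion.** The point holds as a risk that the stated order creates and the stated safeguards do not close. It is not a demonstrated bias. The order itself is certain, since two statements agree on it. The harm through reactive baselines depends on the arm being known before T0 and on a response that differs between arms. The harm through early loss depends on withdrawal that differs between arms.

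Its size cannot be derived from the document. The type I error figures rest on assumed shifts, assumed correlations and equal correlation over time. They show that the group × time test is sensitive to small differential baseline shifts, most of all when repeated measures are highly correlated, and they do not forecast what will happen. Exposure is greatest for pain, fatigue, quality of life, Timed Up and Go and gait speed, and smaller for the Barthel Index as long as assessor blinding holds.

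**What to change.** For all participants not yet randomized, use this order: consent, eligibility check, T0 recorded and locked, then random allocation. Release the arm to the participant and the treating physiotherapist only, and never to the outcome assessor. Replace the formal-enrolment wording in section 2.2 accordingly. Report how many participants were allocated before T0, and give any losses between allocation and T0 by arm.

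A single sentence withholding the arm from everyone until T0 is recorded would be lighter and would close the disclosure route. It would still allow people to be randomized and then lost before any outcome value exists, so the re-ordering is preferable.

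The cost is a short amendment and, because section 2.1 says recruitment is under way, two baseline procedures within one trial. No visits are added, and the sample size stays at 75.
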